## Statistical considerations

### Randomization

The study will employ a 1:2 randomization between Arm 1: Arm 2, based on the stratification factors described in Methods/design section. Patients will be randomized in permuted blocks, with the size of the blocks known only to the statistician. The randomization sequence is known only to the statistician and uploaded into a restricted-access database (REDCap) housed on secure hospital servers at LHSC. Upon enrollment of a patient, the database will be accessed by the trial co-ordinator to obtain the next intervention in the random sequence, for the pertinent stratum, which will then be assigned to the patient.

### Sample size calculation

The sample size calculation is based on the OS results in the SABR-COMET trial. Overall, in that trial, median OS was 28 months in the standard arm and 41 months in the SABR arm. In the patients with 4–5 metastases, median OS in that trial was 7 months in the standard arm and 14 months in the SABR arm. These latter numbers are not reliable, since the number of patients with 4–5 metastases was very small, but they are useful to illustrate that the expected OS will decrease as the number of lesions increases.

In this current trial, we hypothesize that the median OS will be 10 months in Arm 1 and 17 months in Arm 2. In order to detect this difference, with an alpha of 0.05, 80% power, and a 5% dropout rate, 159 patients will be required. The study projects accrual over 60 months with 12 months of additional follow-up. Analysis will take place at least 12 months after the last patient is accrued, once 122 total OS events have occurred.

### Analysis plan

Patients will be analyzed in the groups to which they are assigned (intention-to-treat). De-identified data (except for study number and initials, see confidentiality below) will be transmitted from participating centres via REDCap to be collected centrally where it will be stored on secure hospital servers at LHSC. Source documents will also be uploaded. Research coordinators (clinical trials staff) will perform data checks throughout the trial period and will call participating centres or visit as necessary. PFS and OS will be calculated using the Kaplan-Meier method with differences compared using the stratified log-rank test. Pre-planned subgroup analyses will occur based on the stratification factors. A Cox multivariable regression analysis will be used to determine baseline factors predictive of survival endpoints. For the endpoint of time to new metastases, a Fine and Gray competing risk analysis will be used to account for competing risk of death. Quality of life at 6 months will be measured using FACT-G and EQ-5D-5 L scores, with differences between groups tested using the Student’s t-test. Differences in rates of grade 2 or higher toxicity between groups will be tested using the Fisher’s Exact Test or Chi-Squared test, as appropriate.

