## Follow-up evaluation and assessment of efficacy

### Follow-up Prior to Progression

Patients will be seen every 3 months post-randomization for the first 2 years, and every 6 months until 5 years after treatment (Table 2). At each visit, a history and physical examination will be conducted by the oncologist, and CTC-AE toxicities recorded. The FACT-G and EQ-5D-5 L quality of life questionnaire is to be completed at each visit.

**Table 2 Tab2:** Follow-up Evaluations

Test and Procedures	1–4 weeks post SABR treatment and prior to systemic therapy	3 Months post Randomization	Years 1–2	Years 3–5	First progression or study completion (at 5 years post-randomization) whichever is first
			Every 3 months	Every 6 months	
History and Physical including assessment of side affects			X	X	
CT or MR head, CT chest, abdomen, pelvis			X	X	
Bone Scan			X	X	
Completion of questionnaires (FACT-G and EQ-5D-5 L)			X	X	
Blood Samples for Correlative Studies (i.e studies that are associated with the main study)	X (Arm 2)	X (Arm 1 & 2)			X (Arm 1 & 2)

CT head (or MR head), CT chest, abdomen and pelvis, and bone scans will be repeated every 3 months for the first 2 years, then every 6 months until 5 years have elapsed. Head imaging can be omitted for histologies without a propensity for brain metastases (e.g. prostate), and bone scans may be omitted in patients without bone metastases at presentation. PET scanning may be used in follow-up for patients who were staged with a PET scan for trial entry. In such cases, the PET replaces the CTs of the chest, abdomen, pelvis and the bone scan; brain imaging would still be required for histologies with a propensity for brain metastases.

Since many patients will be receiving systemic therapy and separately-timed imaging may be required to assess response to systemic therapy, attempts should be made to avoid duplication of scans. The imaging requirements herein may be adjusted by ±4 weeks in order to align with scans used to assess response to systemic therapy.

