### Follow-up after progression

After progression, patients randomized to Arm 2 will be considered for salvage SABR if new sites of disease develop, as long as it can be delivered safely, and to a maximum of 10 lesions total (including lesions treated at baseline).

After progression, for patients in either arm, additional visits, imaging or laboratory investigations should be carried out at the discretion of the oncologist. Additional treatment (e.g. further systemic therapy) is at the discretion of the treating oncologists. However, additional treatments, toxicities of study treatment, vital status and quality of life should still be collected, along with any further anti-cancer treatment delivered (e.g. further palliative radiation or systemic therapy), and this may be ascertained remotely (e.g. by phone or mail) to minimize visit burden for patients.

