### Assessment of efficacy

Overall Survival
◦ Defined as time from randomization to death from any causeProgression-free survival
◦ Defined as time from randomization to disease progression at any site or death.◦ Progression is defined as per the Response Evaluation Criteria in Solid Tumors (RECIST) 1.1 guidelines (http://recist.eortc.org/recist-1-1-2/). It can be difficult to distinguish recurrence from fibrosis/pseudoprogression after stereotactic radiation in some locations, such as the lung or brain. In such cases, if the RECIST 1.1 criteria for progression are met, the situation should be counted as progression unless there is imaging follow-up with stability of the imaging findings for at least 6 months.◦ As per RECIST 1.1, when findings of progression are equivocal (e.g. small new lesions of uncertain etiology), the patient should still be followed. If progression is confirmed at the next assessment, the date of progression assigned is the earlier date when progression was first suspected.Time to development of new metastatic lesions
◦ Defined as the time from randomization to the development of new lesions that were not detectable at the time of randomization. In a situation where indeterminate lesions were present at randomization, progression at one of those lesions does not count as a new metastatic lesion.◦ As noted above, as per RECIST 1.1, when findings of new metastases are equivocal (e.g. small new lesions of uncertain etiology), the patient should still be followed. If progression is confirmed at the next assessment, the date of progression assigned is the earlier date when progression was first suspected.Quality of life
◦ Assessed with the Functional Assessment of Cancer Therapy: General (FACT-G) and the EQ-5D-5 LToxicity
◦ Assessed by the National Cancer Institute Common Toxicity Criteria (NCI-CTC) version 4 for each organ treated (e.g. liver, lung, bone)]

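### Fine-Gray, the only comparison named for time to new metastases, cannot by itself show whether SABR changes the rate of spread; recording of new lesions after progression may also differ by arm

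*Protocol article*

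**What the plan says.** Time to new metastatic lesions is a secondary endpoint. Under Assessment of efficacy it is "Defined as the time from randomization to the development of new lesions that were not detectable at the time of randomization". That definition does not end when a known lesion progresses. The Analysis plan names one method for it: "a Fine and Gray competing risk analysis will be used to account for competing risk of death". The stratified log-rank test is named there for PFS and OS only.

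Under Follow-up Prior to Progression, head and body imaging "will be repeated every 3 months for the first 2 years, then every 6 months until 5 years have elapsed". PFS is "Defined as time from randomization to disease progression at any site or death", so growth of a known lesion counts as progression and ends the scheduled phase. Under Follow-up after progression, for both arms, "additional visits, imaging or laboratory investigations should be carried out at the discretion of the oncologist". The same section says "additional treatments, toxicities of study treatment, vital status and quality of life should still be collected", along with further anti-cancer treatment. New lesions are not in that list. It also says that "patients randomized to Arm 2 will be considered for salvage SABR if new sites of disease develop"; Arm 1 has no equivalent provision.

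The Sample size calculation states: "we hypothesize that the median OS will be 10 months in Arm 1 and 17 months in Arm 2".

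**The concern.** Two separate features affect what this endpoint can show.

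First, the Fine-Gray model keeps patients who have died without a new lesion in the risk set. An arm with fewer deaths has more patients alive to develop a new lesion, so its subdistribution hazard is higher even when the rate among living patients is unchanged. The trial is designed on the expectation that SABR lowers mortality.

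Second, deaths are followed to the end, but after progression new lesions are seen only if someone orders a scan. If known lesions progress sooner in the arm where they are not ablated, Arm 1 patients leave scheduled imaging earlier and may die without a new lesion being recorded.

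The Background says that the risk of further distant failure probably rises with the number of metastases, so readers will look to this endpoint to learn whether ablation alters spread. A ratio above 1 could be taken as harm, or a real reduction in the rate could be hidden.

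**Working it through.** **The plan's own figure.** The article gives no figure for this endpoint, so I checked the survival design that supplies the death rates.

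- Hazard ratio: 10/17 = 0.588. Schoenfeld events, 1:2 allocation, two-sided 0.05 (sidedness is not stated), 80% power: (1.96 + 0.842)² / [(1/3)(2/3)(ln 0.588)²] ≈ 125. At the stated 122 events, power is 78.9%.
- Exponential survival with 60 months of uniform accrual plus 12 months gives event probabilities of 0.897 and 0.771, weighted (0.897 + 2 × 0.771)/3 = 0.813. Then 122/0.813/0.95 = 158 patients, against 159 stated.

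The design reproduces, so exponential survival with medians of 10 and 17 months is a fair basis for what follows.

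**Part 1: the model.** Death hazards are μ₁ = 0.693/10 = 0.0693 and μ₂ = 0.693/17 = 0.0408 per month. The new-lesion hazard λ is set equal in both arms. The protocol gives no value for it; I assume 0.03 to 0.06 per month. Cumulative incidence is F(t) = λ/(λ+μ) × [1 − exp(−(λ+μ)t)]. At 24 months:

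- λ = 0.03: Arm 1, 0.302 × (1 − e^−2.38) = 27.4%; Arm 2, 0.424 × (1 − e^−1.70) = 34.6%. Ratio of −ln(1−F): 0.425/0.320 = 1.33.
- λ = 0.06: Arm 1, 0.464 × (1 − e^−3.10) = 44.3%; Arm 2, 0.595 × (1 − e^−2.42) = 54.2%. Ratio: 0.782/0.586 = 1.33.

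The rate of new lesions is identical by construction, so the cause-specific hazard ratio is exactly 1. Fitting Fine-Gray to 600,000 simulated patients with the trial's allocation, accrual and follow-up gives 1.39 at λ = 0.03 and 1.32 at λ = 0.06. Over assumed median times to a new lesion of 4 to 24 months the range is about 1.2 to 1.4. Cause-specific Cox gives 1.00 apart from simulation error.

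These runs use the full survival hazard as the hazard of death before a new lesion. If such deaths are rarer but in the same ratio (0.030 v 0.018, or 0.015 v 0.009 per month, 60-month horizon), the subdistribution ratio falls to 1.13 to 1.27.

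**Part 2: recording after progression.** This is an illustration, not an estimate. Assume λ = 0.06 and death at 0.0693 in both arms, with progression of known lesions (ε) at 0.06 per month in Arm 1 and 0.02 in Arm 2. The ε values have no source in the protocol. If nothing is detected after that progression, observed 24-month incidence is λ/(λ+ε+μ) × [1 − exp(−24(λ+ε+μ))]:

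- Arm 1: 31%. Arm 2: 39%. True value in both: 44%.
- If half of later new lesions are found: (31 + 44)/2 ≈ 38% and (39 + 44)/2 ≈ 42%.

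With 53 and 106 patients, the standard error of a difference of this kind is √(0.38×0.62/53 + 0.42×0.58/106) ≈ 8 points. The 4-point gap is about half a standard error and the 8-point gap about one.

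**Does changing the model suffice?** No. Patients who are no longer scanned but stay at risk until death add person-time in which no event can be seen. In an illustrative model anchored to the earlier trial's PFS medians (6 and 12 months), with equal true rates, the cause-specific ratio was 1.07 to 1.10 with half of later lesions found and 1.19 to 1.21 with none found. Censoring where scheduled imaging ended brought it back to 0.99 to 1.01.

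**The case against.** Fine-Gray is a recognised method and answers a legitimate question. If SABR patients live longer and more of them therefore develop new lesions, a ratio above 1 reports that correctly. This stands: the choice is one of estimand, and the weakness is only that no comparison of rates accompanies it. The cause-specific ratio is not neutral either, because it conditions on being alive, and keeping frailer patients alive can move it. OS and PFS will be reported alongside and give context.

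On recording, the article is a condensed text. The case report form and analysis plan are not shown, so an item absent from the post-progression list may still be collected. The endpoint's definition implies that its date is wanted, and source documents are uploaded. The article also expects many patients to have separately timed scans for systemic therapy, so Arm 1 patients who change treatment might be scanned as often as Arm 2 patients, or more. These points stand, which is why the second part is put as a possibility of unknown size.

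Three stronger readings are tempting and are not supported:

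- A reader might infer that SABR will look worse whatever happens. The shift arises only if SABR lengthens survival or improves control of known lesions; otherwise it vanishes.
- A reader might infer that imaging stops at progression. It becomes discretionary.
- A reader might infer a much larger distortion by combining PFS medians of 6 and 12 months with OS medians of 10 and 17. That gives subdistribution ratios of 1.58 to 2.14 if patients stay at risk to death and, for 159 patients at an assumed 0.025 new lesions per month, a 36% to 48% chance of a significantly worse result for SABR. Those PFS medians come from the earlier trial, where median OS was 28 and 41 months and more than 90% of patients had 1–3 metastases. They do not describe this population.

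**Conclusion.** The concern holds in limited form. With Fine-Gray as the sole comparison, an effect on survival cannot be told apart from an effect on the rate of new lesions. Under the trial's own survival hypothesis and equal new-lesion rates, the subdistribution hazard ratio would be about 1.2 to 1.4, and nearer 1.13 if few patients die before a new lesion appears. This rests on exponential times and on assumed new-lesion hazards.

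The mismatch between an endpoint that runs past progression and an imaging schedule that does not is in the text. Under-recording in Arm 1 is plausible, but its size depends on discretionary scanning and cannot be derived from the article. Only a secondary endpoint is affected; the primary OS analysis and the sample size are not.

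**What to change.** 1. Report the cause-specific hazard ratio for new lesions (log-rank and Cox, stratified by the randomisation factors) as the comparison of the effect on spread. Show cumulative incidences of new lesions and of death beside it. Keep Fine-Gray for comparing cumulative incidence.
2. In the cause-specific analysis, censor patients without a new lesion at their last scheduled scan when scheduled imaging ends because known lesions progressed. Add a sensitivity analysis that treats this progression as a competing event. It bears mainly on the cumulative-incidence results, since the cause-specific estimate is nearly the same either way.
3. Add the date and site of the first new lesion on any routine scan to the data still collected after progression. No additional imaging is implied.

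The cost is a few lines in the analysis plan, one data item and slightly more data entry. Censoring at progression may be informative, because patients whose known lesions grow may also be more prone to new ones. The censored analysis should therefore be shown next to the competing-event version and to one that counts new lesions on any scan.

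### The 6-month quality-of-life comparison is fixed as an unadjusted t-test among survivors: it leaves death unaddressed and ignores scores and stratification factors that could sharpen it

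*Protocol article*

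**What the plan says.** The Analysis plan fixes measure, time point and test: "Quality of life at 6 months will be measured using FACT-G and EQ-5D-5 L scores", "with differences between groups tested using the Student’s t-test". It names no covariate, no stratification, no use of other visits and no treatment of death for this endpoint. In the same paragraph, OS and PFS get a stratified log-rank test, and time to new metastases gets a Fine and Gray analysis because death competes with it.

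More data are collected than the test uses. Under Follow-up Prior to Progression, "Patients will be seen every 3 months post-randomization for the first 2 years", and "The FACT-G and EQ-5D-5 L quality of life questionnaire is to be completed at each visit", so a 3-month score should exist. Under Follow-up after progression, "additional treatments, toxicities of study treatment, vital status and quality of life should still be collected". Progression therefore does not end quality-of-life data; death does.

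For survival, the Sample size calculation states: "we hypothesize that the median OS will be 10 months in Arm 1 and 17 months in Arm 2". Quality of life is part of the trial objective and a listed secondary endpoint. No power figure is given for it.

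**The concern.** The trial is designed on the expectation that SABR prolongs survival. If it does, fewer SABR than control patients will have died by 6 months, and the two groups entering the t-test are no longer the randomised groups. If frailer patients tend both to die earlier and to report lower scores, the control survivors are the more heavily selected and fitter group, and a null or beneficial effect of SABR would look worse than it is.

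The second issue is precision. Each patient's earlier scores, and the two factors that the protocol describes as among the strongest prognostic ones, could reduce residual variance at almost no cost. With 159 patients split 1:2 and further thinned by death, that matters for an endpoint named in the objective.

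Because the method is stated in the article, this concerns a choice that was made, not a detail left to an SAP.

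**Working it through.** **Inputs from the protocol article.** 159 patients, allocation 1:2, hence 53 and 106; medians 10 and 17 months; alpha 0.05, 80% power, 5% dropout; 60 months of accrual plus 12 of follow-up; 122 events. The Sample size calculation also quotes two median pairs from the earlier SABR-COMET trial: 28/41 months overall, and 7/14 months for 4–5 metastases, which it calls unreliable.

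**Assumptions, not in the document.** Exponential survival; two-sided alpha; a correlation rho of 0.3 to 0.7 between a standardised latent quality-of-life score and survival; a correlation r of 0.5 to 0.6 between baseline and 6-month scores.

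**1. The plan's own figure.** The only power figure is for OS. With HR = 10/17 = 0.588, the Schoenfeld formula at 122 events and 1:2 allocation gives 78.9% power. Exponential survival with uniform accrual gives event probabilities of 0.897 (Arm 1) and 0.771 (Arm 2), weighted 0.813. Then 122/0.813 = 150.05, rounded up to 151, and 151/0.95 rounds up to 159. So an exponential model at these medians reproduces the stated sample size.

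**2. Deaths by 6 months**, 1 − 2^(−6/median):

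| Medians (months) | Arm 1 | Arm 2 | Gap (points) |
|---|---|---|---|
| 10 / 17 (hypothesised) | 34.0% | 21.7% | 12.3 |
| 28 / 41 (SABR-COMET overall) | 13.8% | 9.6% | 4.2 |
| 7 / 14 (4–5 metastases) | 44.8% | 25.7% | 19.1 |

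At the hypothesised medians, 53 × 0.660 = 35 and 106 × 0.783 = 83 are alive. About 18 + 23 = 41 of 159 (26%) leave the test through death alone.

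**3. Survivor selection with no true effect.** If survivors are those above a cut-off on a normal latent scale, their mean score is raised by rho × phi(z)/S. Here S is survival at 6 months, z is the normal quantile of 1 − S, and phi is the normal density. At 10/17 months:
- Arm 1: 0.3665/0.6598 = 0.556, times rho
- Arm 2: 0.2938/0.7830 = 0.375, times rho
- Difference: 0.180 × rho, which is 0.05 SD at rho = 0.3 and 0.13 SD at rho = 0.7, against SABR

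At 28/41 the difference is 0.067 × rho, or 0.02 to 0.05 SD. At 7/14 it is 0.283 × rho, or 0.08 to 0.20 SD.

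**4. Against the noise.** SE = sqrt(1/35 + 1/83) = 0.202 SD. The 10/17 shift is therefore 0.054/0.202 = 0.27 to 0.126/0.202 = 0.63 of a standard error.

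**5. Precision.** Detectable difference at 80% power = (1.96 + 0.84) × 0.202 = 0.56 SD. Baseline adjustment multiplies it by sqrt(1 − r²):
- r = 0.5: 0.565 × 0.866 = 0.49 SD, equivalent to 1/0.75 = 1.33 times the patients
- r = 0.6: 0.565 × 0.800 = 0.45 SD, equivalent to 1/0.64 = 1.56 times the patients

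**The case against.** **Early deaths may be fewer than the exponential model implies.** This stands. The article does not state constant hazards, eligibility requires a life expectancy above 6 months, and the Discussion accepts that control survival may be longer than assumed. That is why a range is shown; at the 28/41 medians the shift is at most 0.05 SD.

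**The bias is small and its direction unproven.** This stands too. A reader might infer that the comparison is definitely biased against SABR. The documents do not support that: they give no link between quality of life and survival, and uneven form return could offset or reverse the shift.

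**No baseline questionnaire is collected.** A reader might infer this because neither the pre-treatment investigations nor Table 2 lists one. The inference is not safe. Table 2 covers follow-up only; it has no column for the blood sample at randomisation that Biomarker studies requires. The Experimental arm section mentions a baseline form whose contents are not shown. A condensed article may well leave this to the full protocol.

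**An unadjusted t-test is valid under randomisation.** Leaving out covariates and the 3-month score costs efficiency, not validity, and quality of life among patients alive at 6 months is a describable quantity. Fair, but the article does not say that this is the quantity wanted, and the efficiency is nearly free.

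**A mixed model does not solve truncation by death.** Correct. It treats scores after death as missing, so the fix must address death separately.

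**Conclusion.** The point holds as a badly chosen, stated analysis of a secondary endpoint. The test is restricted to survivors without saying so, although the design's own survival hypothesis, read as exponential, implies about 34% v 22% dead by 6 months (14% v 10% to 45% v 26% across the other quoted medians). Under an assumed correlation of 0.3 to 0.7 and no true effect, the distortion is about 0.05 to 0.13 SD against SABR, or 0.02 to 0.20 SD over all three median pairs. That is modest beside a standard error of about 0.20 SD.

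The precision argument does not depend on the mortality assumptions in kind, though its size depends on the assumed r: a detectable difference of 0.56 SD against 0.49 to 0.45 SD.

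It is worth changing because the change is cheap. It does not touch the primary OS analysis or the sample size.

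**What to change.** 1. Check whether the full protocol already collects FACT-G and EQ-5D-5L at baseline. If not, add them at enrolment, before randomisation.
2. Replace the t-test by a repeated-measures model using the 3- and 6-month scores, with the 6-month contrast as the estimate, adjusted for baseline score, histology group and systemic-therapy group. ANCOVA at 6 months with the same adjustment is a simpler alternative, but it should also draw on the 3-month scores, for example when 6-month forms are missing.
3. State that this main estimate concerns quality of life while alive.
4. Add one supportive rank-based comparison in which death before 6 months ranks worst.
5. Report deaths and form completion by arm beside both results.

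Fix the wording before any quality-of-life data are examined by arm. The cost is slightly more analysis work and possibly one extra questionnaire. The supportive analysis mixes survival with quality of life, so it should be read beside the main estimate and not in place of it.

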### Randomized evidence supporting the oligometastatic state

Two of these four randomized trials were done in the setting of oligometastatic non-small cell lung cancer (NSCLC). In both, patients presented with a primary lung tumor and a limited number of metastatic lesions (1–3 in one trial, 1–5 in the other), and after initial systemic therapy, patients were randomly assigned to standard palliative treatments vs. consolidative ablative treatments to all sites of disease. Both trials were stopped early due to evidence of efficacy, with the ablative treatments achieving a ~ 3-fold improvement in progression-free survival (PFS) [6, 7]. Based on these results, the phase III NRG LU-002 trial is assessing the impact of consolidative ablative therapies on OS.

A third trial, EORTC 40004, examined the impact of an ablative therapy (radiofrequency ablation [RFA]) in patients with colorectal cancer metastatic to the liver. In this trial, patients with a controlled primary tumor and fewer than 10 hepatic metastases not amenable to resection, and with no extra-hepatic disease, were randomized to systemic therapy +/− RFA to all sites of disease [8]. When initially reported [9], the trial showed no difference in OS between arms, but with long-term follow-up (median 9.7 years), a significant difference in OS emerged, with an 8-year OS of 36% in the RFA arm and only 9% in the systemic therapy arm [8].

The fourth trial, Stereotactic Ablative Radiotherapy for the Comprehensive Treatment of Oligometastatic Disease (SABR-COMET) enrolled 99 patients who had controlled primary solid tumors and up to 5 metastatic lesions [10–12]. Patients were randomized in a 1:2 ratio between standard of care (SOC) palliative treatments (Arm 1) vs. SOC + SABR to all sites of disease (Arm 2). The primary endpoint was OS, and the trial employed a randomized phase II screening design, with an alpha of 0.20, in order to provide an initial comparison between arms. More than 90% of patients enrolled had 1–3 metastases. OS was 28 months in Arm 1 and 41 months in Arm 2 (*p* = 0.09), meeting the primary endpoint of the trial. PFS was doubled: 6 months in Arm 1 and 12 months in Arm 2 (*p* = 0.001). SABR was generally well tolerated, with a 29% rate of grade 2 or higher toxicity, although the rate of treatment-related grade 5 toxicity was 4.5%.

Despite this new evidence, many uncertainties remain regarding the oligometastatic state.

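### The crude comparison of grade 2+ toxicity sets no time window and makes no allowance for the longer follow-up expected in Arm 2, so it can be biased towards apparent SABR harm if toxicity keeps accruing.

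*Protocol article*

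**What the plan says.** Toxicity is a named secondary endpoint, graded by NCI-CTC version 4 for the organs treated (Secondary endpoints; Assessment of efficacy). On its analysis, the Analysis plan states: "Differences in rates of grade 2 or higher toxicity between groups will be tested using the" Fisher's exact or chi-squared test. No time point, censoring rule or competing-event rule is attached. The same paragraph does deal with these matters for two other endpoints: time to new metastases has a Fine and Gray analysis because of death, and quality of life is compared at 6 months.

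The Sample size calculation section states the survival hypothesis: "we hypothesize that the median OS will be 10 months in Arm 1 and 17 months in Arm 2".

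On data collection, Follow-up Prior to Progression sets visits every 3 months for 2 years and then every 6 months to 5 years: "At each visit, a history and physical examination will be conducted by the oncologist, and CTC-AE toxicities recorded". After progression the wording narrows. Follow-up after progression says "additional treatments, toxicities of study treatment, vital status and quality of life should still be collected", and allows this to be done remotely.

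**The concern.** A proportion of patients with at least one event depends on the event rate and on how long patients are watched. Two arms with the same rate per month will show different proportions if one is observed longer. Under the trial's own hypothesis Arm 2 is observed longer because its patients live longer, so the more SABR prolongs survival, the more the crude comparison tilts against it.

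The change of wording at progression may add a second imbalance. If the endpoint counts toxicity of any cause, events not attributed to study treatment can be counted only until progression. The background section reports of the earlier phase II trial that "PFS was doubled: 6 months in Arm 1 and 12 months in Arm 2", so that period could be shorter in Arm 1.

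The trial asks whether treating 4 to 10 lesions brings benefit at acceptable toxicity. A toxicity p-value whose false-positive rate rises with efficacy is a weak basis for that judgement.

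**Working it through.** **Inputs from the protocol article.** Median OS is 10 v 17 months. Allocation is 1:2, so 53 v 106 of 159. The size is set "with an alpha of 0.05, 80% power, and a 5% dropout rate, 159 patients will be required". Recruitment is expected to take 60 months and is followed by a further year of observation; the analysis waits for 122 deaths. Visits run to 5 years.

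**Assumptions.** Two-sided alpha, exponential survival, uniform accrual, and no dropout in the exposure calculations. The timing of toxicity is not given in the document, so it is varied.

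**1. The plan's own figures.** The monthly death hazards are ln2/10 = 0.0693 and ln2/17 = 0.0408. The probability of death by the analysis is 1 − [exp(−12λ) − exp(−72λ)]/(60λ) = 0.897 and 0.771. Weighted 1:2 this is 0.813.
- Evaluable patients: 159 × 0.95 = 151. Expected deaths: 151 × 0.813 = 122.8, against 122 stated.
- The Lachin-Foulkes formula gives N = 147.6, and 147.6/0.95 rounds up to 156, with 120 events.
- The Schoenfeld formula gives 126 events. Power at 122 events is 78.9%.

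The design figures are reproduced closely enough to serve as the basis for follow-up time.

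**2. Observation time.** Observation is the smallest of time to death, administrative cut-off (uniform on 12 to 72 months) and 60 months. The means are 12.9 months in Arm 1 and 18.8 in Arm 2, a ratio of 18.8/12.9 = 1.46.

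**3. Identical constant toxicity hazard, observed to death.** At 0.02 per month, about 21% v 29% of patients are affected, and Fisher's test gives p<0.05 in about 14 to 15% of simulated trials, nearly all against SABR. Over 0.01 to 0.04 per month the figure is about 9 to 23%. With equal survival it is about 3 to 4%. Calibrated to the Arm 1 proportion, the false-harm rates (nominal 2.5% in that direction) are:

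| Arm 1 | Arm 2 | False harm, chi-squared | False harm, Fisher |
|---|---|---|---|
| 20% | 27.5% | 16% | 14% |
| 30% | 39.8% | 22% | 20% |
| 50% | 61.6% | 29% | 25% |

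**4. Identical hazard, but only early after randomization** (Arm 1 at 30%, observed to death, chi-squared):

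| Hazard lasts | Arm 2 | False harm |
|---|---|---|
| 3 months | 31.2% | 3.3% |
| 6 months | 32.3% | 4.7% |
| 12 months | 34.4% | 8.1% |
| 24 months | 37.5% | 14.7% |

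**5. Upper bound: observation stops at progression**, using the earlier trial's 6 v 12 months. Mean observation is 8.3 v 14.9 months. Over hazards of 0.01 to 0.04, Fisher's test gives p<0.05 in about 12 to 37% of trials.

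**6. What a remedy does.** With toxicity hazard h and death hazard m, cumulative incidence at time t is h/(h+m) × [1 − exp(−(h+m)t)]. At h = 0.02:
- 6 months: (0.02/0.0893) × (1 − exp(−0.536)) = 9.3% in Arm 1, and (0.02/0.0608) × (1 − exp(−0.365)) = 10.1% in Arm 2.
- 12 months: 14.7% v 17.0%.

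A fixed window therefore removes most of the artefact at 6 months and less of it at 12. A comparison of events per person-month, which targets the same rates as a cause-specific log-rank test, restores the nominal level under identical hazards: false harm in 1.7 to 2.0% of trials and two-sided error of 4.3 to 4.9%.

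**The case against.** The best defence is that the article condenses a longer protocol and that an analysis plan not shown may define a window. Both named tests are compatible with one, and step 6 shows that a 6-month window nearly removes the problem. This stands in part: the text does not say that the proportion is taken over all follow-up. But the article does name the test, and it states a time point or a competing-risk method for neighbouring endpoints and neither for toxicity.

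Second, the size rests on an assumed hazard. SABR is finished within 2 weeks, and if grade 2+ toxicity is mostly early, the distortion is small. This stands, and it limits the finding. On the other side, nothing in the document confines toxicity to an early period: visits run to 5 years, systemic therapy may continue in both arms, and Arm 2 patients may receive further SABR.

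Third, a reader might infer that Arm 1 has only half the window in which toxicity can be counted. The documents do not support that. Study-treatment toxicity is still collected after progression, and the endpoint is defined by treated organ. The 6 v 12 month PFS comes from a trial in which more than 90% of patients had 1 to 3 metastases. The article gives no PFS assumption for 4 to 10 lesions.

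Fourth, no stated decision hangs on this p-value. The safety committee works from its own toxicity thresholds. This stands.

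**Conclusion.** The concern holds in a limited form. As stated, the comparison makes no allowance for the longer observation that the design expects in Arm 2. It can be biased towards SABR harm if two conditions hold: the hypothesised survival benefit is real, and toxicity continues to accrue over follow-up. With a constant hazard of 0.01 to 0.04 per month observed to death, a false significant result occurs in about 9 to 23% of trials. With toxicity confined to the first 3 to 6 months, the gap is about 1 to 2 points and false harm about 3 to 5%. The until-progression range of 12 to 37% is an upper bound, applicable only if the endpoint is all-cause and the earlier trial's PFS carries over.

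A reader might go further and conclude that equal toxicity would necessarily look like SABR harm, or that the p-value could not be interpreted. Neither follows. Even with a constant hazard observed to death, at least three-quarters of trials (100 − 23 = 77%) show no significant difference, and with equal survival this source of bias disappears. The proportion ever affected also remains a valid description of cumulative burden; it is not a comparison of rates per time at risk.

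Severity is low to moderate. Confidence is moderate, because the timing of toxicity is not stated and an analysis plan not shown could set a window.

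**What to change.** In the Analysis plan:
- Make the between-arm comparison an analysis of time to first grade 2+ toxicity from recorded onset dates, with a cause-specific log-rank test, censoring at death, as the test of toxicity rates.
- Report cumulative incidence per arm at 6 months, with 12 months as supportive, treating death as a competing event, with a 95% confidence interval for the difference. Present this as a description of burden, and state that it is a different quantity from the one tested, so the two can disagree.
- Keep crude proportions as description only.

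In the two follow-up sections, reconcile the wording so that one attribution definition for toxicity applies before and after progression in both arms. The choice should be deliberate: an all-cause definition after progression would also take in toxicity from later discretionary systemic therapy.

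The cost is a change of wording, onset dates for grade 2+ events, and slightly more data entry after progression, which the remote contact already allowed can supply. Treatment, sample size and primary endpoint are untouched.
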